# Patient-reported outcomes in terms of swallowing and quality of life after prophylactic versus reactive percutaneous endoscopic gastrostomy tube placement in advanced oropharyngeal cancer patients treated with definitive chemo-radiotherapy: Swall PEG study

**DOI:** 10.1186/s13063-022-06991-6

**Published:** 2022-12-21

**Keywords:** Oropharyngeal squamous cell carcinoma, Head and neck cancer, Endoscopic gastrostomy, Radiotherapy, Patient-reported outcome

## Abstract

**Background:**

Percutaneous endoscopic gastrostomy (PEG) is often used to provide nutritional support in locally advanced head and neck cancer patients undergoing multimodality treatment. However, there is little published data on the impact of prophylactic versus reactive PEG. PEG placement may affect swallowing-related physiology, function, and quality of life. The Swall PEG study is a randomized controlled phase III trial testing the impact of prophylactic versus reactive PEG on patient-reported outcomes in terms of swallowing and quality of life in oropharyngeal cancer patients.

**Methods:**

Patients with locally advanced oropharyngeal cancer receiving chemo-radiotherapy will be randomized to either the prophylactic or reactive PEG tube group. Randomization will be stratified by human papillomavirus (HPV) status and unilateral versus bilateral positive neck lymph nodes. The primary objective of the study is the patient’s reported outcome in terms of swallowing (MD Anderson Dysphagia Inventory (MDADI)) at 6 months. Secondary objectives include health-related quality of life, dosimetric parameters associated with patient-reported outcomes, chemo-radiation toxicities, PEG tube placement complications, the impact of nutritional status on survival and toxicity outcomes, loco-regional control, overall survival, the impact of HPV and tobacco smoking on survival outcomes and toxicities, and the cost-effectiveness of each treatment strategy.

**Discussion:**

Findings from this study will enhance clinical evidence regarding nutritional management in oropharyngeal cancer patients treated by concurrent chemo-radiation.

**Trial registration:**

ClinicalTrials.gov NCT04019548, study protocol version 2.0_08/08/2019. Registered on 15 July 2019

## Background

Oropharyngeal squamous cell carcinoma (OPSCC), the most common malignancy among the head and neck sites, arise in the tonsils, pharyngeal wall, soft palate, base of tongue, and vallecula. Around 98,412 new cases were diagnosed worldwide in 2020 resulting in 48,143 deaths [1].

### Treatment

The treatment of OPSCC has evolved over time, especially since the discovery of the HPV entity. Although a monotherapy of either surgery or radiation therapy (RT) remains the main treatment modality for early-stage OPSCC, concurrent chemoradiation therapy (CCRT) has largely replaced RT alone for locally advanced disease. The use of CCRT and intensified RT was implemented widely in the late 1990s and early 2000s [2–6]. Based on four large randomized trials, conventionally fractionated external beam RT with concurrent administration of three cycles of high-dose cisplatin (100 mg/m^2^) given once every 3 weeks represents the current standard in definitive and adjuvant treatment of locally advanced head and neck squamous cell carcinoma (HNSCC), as it results in significantly better locoregional control (LRC) and overall survival (OS) relative to RT alone [4, 5, 7, 8]. However, the toxicity of this approach is a serious limitation which precludes further treatment intensification and thereby further improvement in outcome [9].

### Treatment-related side effects and patient-reported outcomes

With the increasing recognition of the side effects of modern combined modality treatment for HNSCCs on the one hand and its increased cure rates (particular for HPV-initiated oropharyngeal cancers) on the other hand, it is important to measure and reduce the late treatment-related toxicity. Evaluation of side effects and patient-reported outcomes (PROs) have been developed empirically for over more than 30 years. At the same time multiple grading scales dating from the nineties such as World Health Organization (WHO) scale; Radiation Therapy Oncology Group/European Organization for Research and treatment of Cancer (RTOG/EORTC); Late Effects Normal Tissue Task Force (LENT)—Subjective, Objective, Management, Analytic (SOMA) scales; and Common Terminology Criteria for Adverse Events (CTCAE) are used in parallel to “objectively” report on treatment-related side effects [10]. Each system uses slightly different criteria, with some focused on symptoms and others on interventions, leading to potential discrepancies when scoring toxicities in different systems. The CTCAE scale is widely accepted as the standard classification and severity grading scale for adverse events in clinical trials including multimodality approach. Furthermore, the CTCAE scale is periodically revised, with Version 5.0 (November 27, 2017) being the latest for now. However, this scale is not very detailed on RT toxicity. On the other hand, PROs, defined as a health outcome directly reported by the patient, cover the *subjective* domain of the side effects. Exploratory work suggests that patient-reported outcome measurements (PROMs) can be used with a high degree of subject engagement and compliance [11]. These Quality of life (QOL) questionnaires measure a subjective concept, reflecting a subject’s sense of well-being, incorporating domains such as physical, functional, social, and emotional well-being. Their development and use are based on the science of psychometrics [12]. The EORTC QOL-HN35 questionnaire, specifically developed for HNSCCs patients, was validated in the 1990s and is nowadays used as a worldwide standard [13]. Its major advantage is the symptom severity of HNSCCs and its treatment-specific adverse effects (e.g., swallowing problems, xerostomia and changes in speech, etc.) being assessed by the subject. The EORTC QOL group conducted two systematic reviews concluding that the extensive use of HN35 module throughout the world has demonstrated robust psychometric features in different languages [14, 15]. However, some reported methodological problems suggested that the instrument could be improved in some areas, while studies investigating targeted and/or multimodal therapy consider some QOL issues specific to these treatments not to be covered by the HN35 module. Therefore, the module has been adapted into the EORTC QOL-HN43, of which the final validation (phase IV) has been completed in February 2017 [16]. In order to assess the swallowing function, one of the validated instruments is MD Anderson Dysphagia Inventory (MDADI). It is a self-administered questionnaire evaluating the impact of dysphagia on the QOL of patients with head and neck cancer [17].

### Swallowing-related outcomes and the effect of prophylactic PEG tube placement

In HNSCC treatment, swallowing is one of the most important toxicities in terms of QOL [18]. Langendijk et al. conducted a study with assessments by the EORTC/RTOG toxicity scale and the EORTC QLQ 30 and HN35 modules at 6, 12, 18, and 24 months after the end of RT. All patients (*n* = 425) were treated by RT alone (3D conformal without attempts to spare the salivary glands) or in combination with chemotherapy and/or surgery for HNSCCs of the oral cavity, oropharynx, nasopharynx, hypopharynx, and larynx. They concluded a higher toxicity score to be correlated with significant impairment of QOL in general. The degree of xerostomia and dysphagia had a significantly greater impact on QOL compared to other toxicities as late reactions of the skin, subcutaneous tissue, mucous membrane, and larynx, with xerostomia being more frequent while dysphagia having the bigger impact. In order to prevent malnutrition and dehydration following these frequent side effects, some centers perform percutaneous endoscopic gastrostomy (PEG) tubes placed prophylactically (pPEG). According to recent ESPEN guidelines, enteral feeding is strongly recommended in patients with obstructing head and neck cancer with expected severe radiation-induced oral mucositis. However, the effect of pPEG on clinical outcome has not been investigated in randomized trial [19]. A recent research has suggested that pPEG use may negatively affect swallowing physiology, function, and/or QOL, especially in the long term [20]. The evaluation of swallowing function was performed with various subject- and physician-rated instruments, and there is still a lack of data from clinical trials systematically collecting information on swallowing via instrumental objective measurements (e.g., video fluoroscopic swallowing examination, manometry). The available data regarding the frequency and severity of dysphagia and swallowing-related outcomes vary and are inconclusive; hence, the impact of pPEG use on swallowing and swallowing-related outcomes remains unclear [21]. The choice between prophylactic and reactive placement of a PEG tube is generally based on the experience of an individual institution rather than on a high level of evidence [22, 23]. A prospective randomized trial is the most robust way to answer the question on which modality provides better functional outcome for HNSCC patients.

## Methods/design

### Study design

This is a multi-institutional prospective, randomized, phase III clinical trial evaluating PROs on swallowing using the MDADI, 6 months after the end of CCRT in patients randomized to either the pPEG tube group or the reactive PEG tube group.

The study design is illustrated in Fig. 1.

**Fig. 1 Fig1:**
[figure not shown]
Study design

### Assignment of intervention

#### Sequence generation

The patients will be randomly assigned at the Institut Jules Bordet with a 1:1 allocation as per a computer-generated randomization schedule stratified by institution, HPV status (negative, positive), and lymph node metastasis (no lymph node metastasis or unilateral lymph node metastasis vs bilateral lymph node metastasis).

#### Concealment mechanism

The use of a web-based allocation system and the minimization process will ensure that the allocation sequence is concealed until the intervention is assigned.

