### Sample size calculation

The registered subjects are randomized (1:1) between pPEG and rPEG tube placement. The randomization will be stratified by the HPV status and unilateral versus bilateral metastatic neck lymph nodes. The MDADI is a patient-reported outcome scale, and it is composed of 19 items: emotional (6 questions), functional (5 questions), and physical (8 questions) scored from 1 to 5 plus one global question. The mean score of the 19 items will be multiplied by a factor of 20 to obtain a MDADI total score, which ranges from 20 (extremely low functioning) to 100 (high functioning). A difference of 10 points are considered as the minimal clinically important difference (MCID) in the MDADI, as it corresponds to the difference observed between patients taking soft food versus tube feeds [24, 25]. The study’s aim is to detect a difference of at least 10 points between the two arms in the MDADI composite score. Considering an average MDADI composite score of 50 in the prophylactic arm and 60 in the reactive arm (standard deviation 17.5), 100 subjects are needed to detect a significant difference between the two arms (power of 0.80, alpha 0.05 two-sided test). Taking a 10% drop-out rate into account, a total of 110 randomized subjects will be required. To assess survival data, we will use Kaplan-Meier curves with log-rank test. Cox’s proportional hazard model will be used for calculating hazard ratios. To compare continuous outcome variables between the two arms, *t*-test or Wilcoxon test will be used. Categorical variables between the two arms will be analyzed with the chi-square test or Fisher exact test. No data imputation of missing values will be performed. Stratified analyses by HPV status (negative, positive) will be performed as exploratory analyses.

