### Patients’ characteristics

Newly diagnosed, histologically confirmed primary OPSCC patients, candidate for curative intent RT and systemic treatment, will be included in the study. The patients for this study are recruited in the Jules Bordet Institute, Centre Hospitalier Universitaire Saint- Pierre and Hôpital Erasme—Clinique Universitaire de Bruxelles. Inclusion and exclusion criteria are listed in Table 1.

**Table 1 Tab1:** Study inclusion, exclusion, and drop out criteria

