**Inclusion criteria**	
• Age ≥ 18 years old	
• ECOG performance status ≤ 2	
• Newly diagnosed, histologically confirmed primary, stage III or IV HPV-negative^a^ oropharyngeal cancer, or T3-4/ N0-3 and T0-4/N1-3 HPV-positive oropharyngeal cancer according to the UICC TNM 8th edition • Candidate for curative intent CCRT	
• No prior or current anticancer treatment for the HNSCC (e.g., neo-adjuvant chemotherapy, surgery)	
• No contraindication for cisplatin-based chemotherapy	
• Ability to understand and complete the questionnaires (language proficiency, cognitive functioning as judged by principal investigator upon screening)	

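### The article names two allocation methods and two lists of balancing factors, credits minimisation with concealment, and states a primary comparison that ignores the factors

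*Protocol article*

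**What the plan says.** Four places in the protocol article describe the randomisation.

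- **Sequence generation**: 1:1 allocation at the coordinating institute by a "computer-generated randomization schedule stratified by institution, HPV status (negative, positive), and lymph node metastasis". The nodal factor has two levels: "no lymph node metastasis or unilateral lymph node metastasis vs bilateral lymph node metastasis".
- **Concealment mechanism**, the next paragraph: "The use of a web-based allocation system and the minimization process will ensure that the allocation sequence is concealed until the intervention is assigned".
- **Abstract, Methods**: "Randomization will be stratified by human papillomavirus (HPV) status and unilateral versus bilateral positive neck lymph nodes".
- **Sample size calculation**: "The randomization will be stratified by the HPV status and unilateral versus bilateral metastatic neck lymph nodes".

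Two further places bear on these. Table 1 admits "T3-4/ N0-3 and T0-4/N1-3 HPV-positive oropharyngeal cancer according to the UICC TNM 8th edition", so HPV-positive T3-4 patients without nodal disease can enter. The Patients' characteristics section names three recruiting hospitals: "The patients for this study are recruited in the Jules Bordet Institute, Centre Hospitalier Universitaire Saint- Pierre and Hôpital Erasme" being the third in that list.

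On analysis, the Sample size calculation says that continuous outcomes will be compared between arms with a t-test or a Wilcoxon test. MDADI at 6 months, the primary outcome, is a continuous score and falls under that sentence. The only stratified analyses mentioned are exploratory, by HPV status.

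**The concern.** A stratified schedule and minimisation are different procedures. With a schedule, the assignments within each stratum are generated beforehand. With minimisation, each assignment is computed from the factors and allocations of patients already enrolled, so no stratified list exists. The article names both in adjacent paragraphs.

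The factor lists also differ. One has institution and the others do not. One places node-negative patients with unilateral disease, and the others have no level for them.

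The concealment sentence adds a conceptual error. Minimisation is a way of balancing covariates. Keeping the next assignment from the recruiting team until the patient is entered is done by the central web-based release.

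At stake is how the primary result should be analysed and judged. Balancing arms on prognostic factors makes the difference in means less variable, but a test that ignores the factors does not count that gain. To carry the factors into the analysis, one has to know which they are, and the article gives two answers.

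**Working it through.** **1. The plan's own figure.** Inputs from the Sample size calculation: difference 10, SD 17.5, two-sided alpha 0.05, power 0.80.

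n per arm = 2 × (1.960 + 0.842)² × 17.5² / 10² = 48.07, so 49 per arm and 98 in total. The t-distribution version gives 49.05, so 50 per arm and 100 in total, as stated. 100 × 1.1 = 110 is the stated randomised number; dividing instead, 100 / 0.9 = 111.1, gives 112. The sample size reproduces, and this point does not turn on it.

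**2. The descriptions side by side.**

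| Place | Method | Institution | HPV | Nodal levels |
|---|---|---|---|---|
| Sequence generation | computer-generated stratified schedule | yes | yes | none or unilateral / bilateral |
| Concealment mechanism | minimisation | – | – | – |
| Abstract, Methods | stratified | no | yes | unilateral / bilateral |
| Sample size calculation | stratified | no | yes | unilateral / bilateral |

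**3. How different the two factor lists are.** With three hospitals:

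- Sequence generation: 3 × 2 × 2 = 12 cells; 110 / 12 = 9.2 patients per cell on average.
- Abstract and Sample size calculation: 2 × 2 = 4 cells; 110 / 4 = 27.5 per cell, and none for a node-negative patient.

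**4. What the unadjusted test costs.** The article does not say how much of the MDADI variance the factors explain, so R² is an assumption, shown over a range. Suppose the factors are well balanced. The unadjusted standard error at 50 per arm is 17.5 × √(2/50) = 3.50. The true standard error is about 3.50 × √(1 − R²).

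- Ratio of reported to true standard error: 1 / √(1 − R²).
- Actual two-sided error of the unadjusted test: 2 × [1 − Φ(1.960 / √(1 − R²))].
- Power, unadjusted: Φ[(10 − 1.960 × 3.50) / true SE].
- Power, adjusted: Φ[10 / true SE − 1.960].

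| Assumed R² | True SE | Ratio | Actual error, unadjusted | Power, unadjusted | Power, adjusted |
|---|---|---|---|---|---|
| 0 | 3.50 | 1.00 | 0.050 | 0.815 | 0.815 |
| 0.05 | 3.41 | 1.03 | 0.044 | 0.821 | 0.834 |
| 0.10 | 3.32 | 1.05 | 0.039 | 0.828 | 0.853 |
| 0.20 | 3.13 | 1.12 | 0.028 | 0.842 | 0.892 |

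These are normal approximations and ignore the few degrees of freedom that the model spends.

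**5. Those degrees of freedom.** Institution takes 2, HPV 1 and nodes 1, so 4 in all. Residual degrees of freedom at 100 evaluable patients fall from 98 to 94.

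**The case against.** Most of this can be read as loose drafting. Trial articles often call minimisation factors stratification factors, and "schedule" may simply mean a central computer procedure, so the Sequence generation and Concealment paragraphs may describe one system. The Abstract and the sample-size sentence may be shortened versions of the fuller list. This has force: two rival procedures are not shown to exist. It does not remove the need to correct the text, because a reader cannot tell which method was run, and the sample-size sentence stands in the Methods, where abbreviation is harder to excuse than in an abstract.

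A reader might infer that node-negative patients cannot be randomised. The documents do not support that, since Sequence generation gives them a level. The gap is confined to the Abstract and the Sample size calculation.

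A reader might also infer that concealment fails, or that allocation is predictable in an unblinded trial with a self-reported outcome. That is not supported either. The sentence credits the web-based system jointly with minimisation, and a central web release can conceal. The Implementation section places randomisation after consent and baseline assessment. Predictability under minimisation depends on whether there is a random element. The article is silent on this, and the full protocol may settle it.

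Finally, covariate adjustment might be called a matter for the analysis plan. If the article were silent, that would be so. It does, however, state the test for continuous outcomes, and the stated test leaves the factors out.

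**Conclusion.** The point holds as an inconsistency in the description of the design, together with one misattribution and one stated analysis that does not follow the randomisation. The method (schedule or minimisation), the factor list (three or two, 12 cells or 4) and the nodal coding (with or without a place for node-negative patients) each need one answer. Crediting minimisation with concealment is wrong as written, but it is an error of attribution and not evidence of a failure.

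The analytic consequence is modest and runs in the conservative direction: standard errors about 3% to 12% too wide for an assumed R² of 0.05 to 0.20, and none if the factors do not predict MDADI. A reader might fear an inflated false-positive rate from ignoring the factors. The calculation shows the opposite, an actual error below 0.05 and some power forgone. The size rests on the assumed R² and on good balance being achieved. The planned 100 and 110 patients stand.

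**What to change.** 1. State, in Sequence generation and in Concealment mechanism, the one allocation method that the system actually uses. Enrolment began in December 2019, so this is a matter of reporting what was implemented.
2. Repeat the Sequence generation factor list (institution; HPV status; none or unilateral versus bilateral nodes) in the Abstract and the Sample size calculation, after confirming that it matches the system.
3. Attribute concealment to the central web-based release alone.
4. For the primary MDADI comparison, replace the unadjusted t-test or Wilcoxon test with a linear model with terms for arm, institution, HPV status and nodes in those levels.

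The cost is minor wording in four places and 4 degrees of freedom, with no change to the sample size. No change to the allocation system itself is asked for, since the article does not show that anything in it is deficient.

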#### Implementation

Patients who give consent to participation and fulfil the inclusion criteria will be randomized. For this, Head and Neck Cancer teams will contact the local clinical study coordinator who will schedule the baseline assessment. Randomization will occur after the baseline assessment is completed. The clinical study coordinator is responsible for communicating the allocated group to the clinician who will inform the participant.

### Study objectives and statistical analyses

The primary goal of this study is to assess and analyze the PROs in terms of swallowing (MDADI) at 6 months after the end of CCRT in subjects randomized to either the pPEG tube group or the rPEG tube group.

The secondary objectives are as follows:Health-related QOL (HRQOL; EORTC QLQ-C30; EORTC QLQ-H&N43 module) and Functional Assessment of Cancer Therapy-Head and Neck (FACT-HN).Dosimetric parameters associated with PROs.CCRT-related toxicities and PEG tube placement complications.The impact of nutritional status on survival and toxicity outcomes.Clinical and radiological tumor response.Loco-regional control (LRC), distant recurrence (DR), second primaries (SP), disease-free survival (DFS), disease-specific survival (DSS), and overall survival (OS). Time to event variable will be assessed from the day of randomization to the day of the first record of any of the considered events.The impact of HPV and tobacco smoking on these secondary endpoints.Cost-effectiveness of each treatment strategy.Clinical validation of cancer prediction models available at www.predictcancer.org.

### Sample size calculation

The registered subjects are randomized (1:1) between pPEG and rPEG tube placement. The randomization will be stratified by the HPV status and unilateral versus bilateral metastatic neck lymph nodes. The MDADI is a patient-reported outcome scale, and it is composed of 19 items: emotional (6 questions), functional (5 questions), and physical (8 questions) scored from 1 to 5 plus one global question. The mean score of the 19 items will be multiplied by a factor of 20 to obtain a MDADI total score, which ranges from 20 (extremely low functioning) to 100 (high functioning). A difference of 10 points are considered as the minimal clinically important difference (MCID) in the MDADI, as it corresponds to the difference observed between patients taking soft food versus tube feeds [24, 25]. The study’s aim is to detect a difference of at least 10 points between the two arms in the MDADI composite score. Considering an average MDADI composite score of 50 in the prophylactic arm and 60 in the reactive arm (standard deviation 17.5), 100 subjects are needed to detect a significant difference between the two arms (power of 0.80, alpha 0.05 two-sided test). Taking a 10% drop-out rate into account, a total of 110 randomized subjects will be required. To assess survival data, we will use Kaplan-Meier curves with log-rank test. Cox’s proportional hazard model will be used for calculating hazard ratios. To compare continuous outcome variables between the two arms, *t*-test or Wilcoxon test will be used. Categorical variables between the two arms will be analyzed with the chi-square test or Fisher exact test. No data imputation of missing values will be performed. Stratified analyses by HPV status (negative, positive) will be performed as exploratory analyses.

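### Kaplan-Meier is the only estimator of event probability named for time-to-event data, although four of the six endpoints have competing deaths whose handling is not stated, and the main comparison is not tied to the randomisation strata

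*Protocol article*

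**What the plan says.** Under Study objectives and statistical analyses, the protocol article groups six time-to-event outcomes in one secondary objective: "Loco-regional control (LRC), distant recurrence (DR), second primaries (SP), disease-free survival (DFS), disease-specific survival (DSS), and overall survival (OS"). One rule covers all six: "Time to event variable will be assessed from the day of randomization to the day of the first record of any of the considered events". It fixes the time origin. It does not say, endpoint by endpoint, whether death without the event counts as an event, is censored or is a competing event.

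The methods are in the section Sample size calculation: "To assess survival data, we will use Kaplan-Meier curves with log-rank test", and then "Cox’s proportional hazard model will be used for calculating hazard ratios". No strata or covariates are given for either. No cumulative-incidence, cause-specific or subdistribution method is named.

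HPV appears in three places:
- as a secondary objective: "The impact of HPV and tobacco smoking on these secondary endpoints";
- in the analysis text: "Stratified analyses by HPV status (negative, positive) will be performed as exploratory analyses";
- as a randomisation factor. Sequence generation describes a "computer-generated randomization schedule stratified by institution, HPV status (negative, positive), and lymph node metastasis", while Sample size calculation says "The randomization will be stratified by the HPV status and unilateral versus bilateral metastatic neck lymph nodes". The second list omits institution, but HPV and nodal status are in both.

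**The concern.** Kaplan-Meier suits overall survival and disease-free survival, where death from any cause is itself an event. Distant recurrence, second primary and cancer-specific death are different, because a patient who dies of something else can no longer have the event. The same holds for loco-regional failure unless death is counted as failure, which the article does not say. A Kaplan-Meier curve that censors those deaths treats the patient as still able to have the event later. Its complement is then a risk in a hypothetical population without other-cause death, and it exceeds the proportion of patients who actually have the event.

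Competing death is plausible here. Eligibility includes stage III-IV HPV-negative disease and ECOG status up to 2, smoking is a factor of interest, and study assessments run to 36 months after treatment. At stake are the absolute risks reported by arm. The cost-effectiveness analysis and the validation of prediction models, both listed objectives, would also be affected if they draw on these events.

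The second part concerns the comparison of arms. The Background links HPV-related disease to higher cure rates, and HPV is a randomisation factor, yet the main log-rank and Cox analyses are not described as using it. Omitting a strong prognostic factor from a Cox model pulls the hazard ratio towards 1 when a true effect exists.

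**Working it through.** **The plan's own figure.** The only sample-size figure is for MDADI at 6 months: difference 10, SD 17.5, two-sided alpha 0.05, power 0.80. The normal formula gives 2 × (1.96 + 0.8416)² × 17.5² / 10² = 48.1, so 49 per arm and 98 in total. The t-test solution is 49.05, so 50 per arm and 100 in total, as stated. Dividing by 0.90 for drop-out gives 109 (from 98) to 112 (from 100), against the stated 110. The figure reproduces, and nothing below changes it. The article gives no event rate, competing-death rate, hazard ratio or event count for any time-to-event endpoint.

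**Formula.** With constant cause-specific hazards h1 (event) and h2 (competing death) over a horizon T:
- one minus Kaplan-Meier, competing deaths censored: e = 1 − exp(−h1·T)
- net probability of competing death: c = 1 − exp(−h2·T)
- cumulative incidence: CIF = h1/(h1 + h2) × [1 − exp(−(h1 + h2)·T)]

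Given e and c, the CIF does not depend on T under this model.

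**Worked case.** Take e = 20% and c = 10%. Then h1·T = −ln 0.80 = 0.2231 and h2·T = −ln 0.90 = 0.1054. CIF = 0.2231/0.3285 × (1 − 0.80 × 0.90) = 0.679 × 0.28 = 19.0%. The excess is 1.0 point.

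**Range (all inputs assumed).** Each cell gives the CIF, with the excess of one minus Kaplan-Meier in percentage points in brackets.

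| One minus KM | c = 5% | c = 10% | c = 20% | c = 30% |
|---|---|---|---|---|
| 10% | 9.75% (0.25) | 9.50% (0.50) | 8.98% (1.02) | 8.44% (1.56) |
| 20% | 19.51% (0.49) | 19.02% (0.98) | 18.00% (2.00) | 16.93% (3.07) |
| 30% | 29.29% (0.71) | 28.56% (1.44) | 27.07% (2.93) | 25.50% (4.50) |

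In relative terms the overstatement is about 2% to 19%.

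**Additivity check.** With e = c = 30%, the two complements of Kaplan-Meier add to 60%, but the all-cause failure probability is 1 − 0.70 × 0.70 = 51%. The two cumulative incidences add to 25.5% + 25.5% = 51%, as they must.

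**Heavier assumptions, T = 3 years.**
- h1 = 0.15, h2 = 0.10 per year: 36.2% against 31.7%, an excess of 4.5 points.
- h1 = 0.15, h2 = 0.20: 36.2% against 27.9%, an excess of 8.3 points.
- h1 = 0.03, h2 = 0.15 (a rarer event such as second primary): 8.6% against 7.0%, about 24% relative.
- h1 = 0.03, h2 = 0.25: 8.6% against 6.1%, about 41% relative.

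Competing hazards of 0.20 and 0.25 per year mean net competing death of 1 − exp(−0.60) = 45% and 1 − exp(−0.75) = 53% at 3 years. That is high for patients treated with curative intent, so these cases mark an upper end.

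**Stratification.** No arithmetic applies. Both descriptions of the randomisation include HPV and nodal status. The sentences on the log-rank test and the Cox model mention neither, and the only stratified analysis named is the exploratory one by HPV.

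**The case against.** The strongest reply is that the stated comparisons of arms are sound. A log-rank test or Cox model that censors competing deaths validly compares cause-specific hazards, and Cox regression is named directly after Kaplan-Meier. That stands: it confines the first part of the point to curves and absolute risks. A reader might infer that Kaplan-Meier with log-rank is the whole plan for these endpoints; the Cox sentence shows otherwise.

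Second, the article does not say that other-cause deaths will be censored or that one minus Kaplan-Meier will be reported as an incidence. If death counted as an event for a given endpoint, the bias would not arise there. This also stands, so the overstatement is conditional. It is not a remote condition, however. Disease-specific survival cannot count other-cause death as an event without becoming overall survival, and no other estimator is offered.

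Third, a reader might infer that HPV is ignored, or that an unstratified test has been chosen. The text supports neither. HPV is a randomisation factor, a secondary objective and the subject of exploratory stratified analyses, and on stratification of the main tests the article is silent.

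Fourth, a condensed article may leave strata and covariates to the full protocol or analysis plan. That weakens the stratification part. It weighs less on the first part, because the article does name an estimator, and that estimator does not by itself fit four of the six endpoints it covers.

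Finally, all these endpoints are secondary and no power is claimed for them, so loss of power defeats no stated design target.

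**Conclusion.** The point holds in a limited, conditional form. Kaplan-Meier is the only estimator of event probability named, and the handling of death without the event is not stated for loco-regional control, distant recurrence, second primaries or disease-specific survival. If other-cause deaths are censored, the direction of the bias is certain: reported risks are too high. The size cannot be fixed from the article. Under constant hazards it is about 0.25 to 4.5 percentage points for an assumed one minus Kaplan-Meier of 10-30% and competing death of 5-30%. It reaches 8.3 points only under the heaviest case shown.

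It would go too far to conclude that published rates will be wrong or that the hazard comparisons are invalid. On HPV, the supported statement is that the main comparison is not described as using the randomisation strata and that stratified analysis by HPV is exploratory. No size was computed for this part, which is the weaker of the two. The primary MDADI analysis and the 110 patients are untouched.

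**What to change.** - Keep Kaplan-Meier for overall survival and disease-free survival.
- For loco-regional failure, distant recurrence, second primary and cancer-specific death, name the competing event for each, report Aalen-Johansen cumulative incidence by arm, and compare arms with cause-specific Cox models. Gray's test can be given as support.
- Stratify or adjust the main log-rank and Cox comparisons for HPV and nodal status, the two factors common to both descriptions of the randomisation. Say whether institution, which only Sequence generation lists, is also used.

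The cost is a few sentences and slightly more analysis work with standard software. No new data are needed beyond date and cause of death, which disease-specific survival already requires. The downside is sparse strata: two HPV levels by two nodal levels give four strata, on average 110/4 = 27.5 patients each, and some will be smaller. Where events are few, covariate adjustment is the easier alternative to stratification.
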